#### **Patient satisfaction (Appendix 2)**

Patient satisfaction will be evaluated for each participant of the care pathway, directly after the patient leaves the care pathway. A preliminary analysis from a recently performed study by [name] (MD) et al. showed some common themes for patients presenting to the ED. These main domains include:

1. relief of symptoms (degree of relief and symptoms, duration until symptom relief, impact on function)
2. understanding the diagnosis and cause of symptoms, understanding prognosis
3. presence and understanding of the diagnostic, therapeutic and follow-up plan
4. reassurance

These domains will be evaluated for patients in the care pathway as well.

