**Intervention:** If feasible, an ED-coach (passive or active form) will be appointed to each participant of the care pathway. The NSC will be evaluated in-depth, the patient will undergo APOP-screening during triage and if indicated, a comprehensive geriatric assessment will be performed after discharge from the ED at another department. The patient will be seen by a specialist or experienced resident in training at the ED, who will order a standard set of diagnostic tests and review the results. The APOP-risk score will guide further actions in the care pathway. A verification of the medication list will be performed <24 hours and a review of the medication will follow during admission.

**Control cohort:** Recruitment of controls will occur before implementation of the care pathway and on workdays between Monday – Friday from 11:00 am – 20:00 pm. The study period is estimated at approximately 6 months, according to study protocol. Each participating hospital will inform participants regarding their policy on data collection prior to implementing the care pathway. Data for controls within hospitals with access to CTcue will be collected retrospectively. The other participating hospitals will include eligible patients prospectively for the same estimated study period. After 30 days, the research nurse will evaluate complications that occurred after the patient leaves the care pathway.

**Main study parameters/endpoints:** Main endpoints are to evaluate the length of stay at the ED (ED-LOS) and exploring patient satisfaction on 4 established domains. Secondary objectives are evaluating the length of stay at the hospital (HOSP-LOS), discharge destination, medical diagnosis (at admission versus discharge), frequency of readmissions / revisits, 30-day mortality, loss of functional

status and costs-effectiveness of the care pathway. Study parameters are age, gender, main non-specific complaint, main diagnosis at ED-arrival and discharge, way of arrival (per ambulance, public transportation, etc.), main domain of NSC (somatic, nutrition, psychosocial, functional, mobility, falls), living situation (independent, care at home), diagnostic tests, specialist seeing the patient and consulting specialists and ED-logistics (time of arrival at ED, duration of triage, triage colour).

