Studies have shown that patients with NSCs have different characteristics compared to patients with specific complaints (SCs) [4]. Patients with NSCs have more comorbidities, use more medications, are at a higher risk of functional decline due to longer hospitalization and have a higher 30-day mortality rate compared to patients with SCs. Undertriage and unnecessary testing often contribute to a prolonged ED stay and frequent readmissions [5]. Furthermore, clinical experience of the health care provider seeing the patient with NSCs impacts diagnostic accuracy [6]. We aim to implement an integrated care pathway in different emergency departments of the Brabant area, focused on streamlining the care of patients with NSCs at the ED. This will be accomplished by evaluating the NSC in-depth (primary care), performing APOP (triage at the ED), screening certain domains of the CGA if a patient is high-risk according to APOP (somatic, nutrition, psychosocial, functional, mobility, falls), performing a standard set of diagnostic tests (at least: ECG, lab, urinalysis, X-thorax and bladder scan) and providing ‘specialized care’, as described in the methods section. In this care pathway, we will guide actions according to the APOP-risk score. After admission, a verification and review of the medication list will be performed. We hypothesize that the care pathway will primarily improve patient satisfaction and reduce the ED-length of stay. Reduced hospital length of stay, decreased 30-day mortality, improved functional status (daily activities, mobility, cognition), a reduction of (re-)admission rates for older adults with NSCs and reduced costs of care for this patient population might follow as a result of implementing this care pathway.

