## **3. OBJECTIVES**

1. The **primary objectives** of the care pathway are to evaluate:

- Length of stay at the ED (ED-LOS)
- Patient satisfaction on 4 domains

1. relief of symptoms (degree of relief and symptoms, duration until symptom relief, impact on function)
2. understanding the diagnosis and cause of symptoms, understanding prognosis
3. presence and understanding of the diagnostic, therapeutic and follow-up plan
4. reassurance during ED-stay

2. The **secondary objectives** of the care pathway are to evaluate:

- Length of stay at the hospital (HOSP-LOS)
- Discharge destination
- Medical diagnosis (at admission versus discharge)
- Frequency of readmissions / revisits
- 30-day mortality
- Loss of functional status
- Costs-effectiveness of the care pathway

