### **5.1.4 Control group**

For patients included in the study as controls, the same inclusion and exclusion criteria apply.

Controls will not be specifically asked for informed consent, as each participating hospital will sign a form to collect data for control patients prior to implementing the care pathway. Additionally, it is the responsibility of each participating institution to inform their patients on the policies regarding data collection in study settings.

Obtaining the retrospective control-group will be done by CTcue, if possible. CTcue is a search engine in which unstructured data from an Electronic Health Record (EHR) can be easily found by adding specific queries in to the search engine. These data will be retrieved anonymously according to our defined in- and exclusion criteria, study parameters and endpoints. Specialists at the ED will be unaware of the patients functioning as controls during this study, since data for controls will be collected retrospectively. After 30 and 90 days, the research nurse will evaluate complications that occurred after the patient leaves the care pathway.

In the participating hospitals without access to CTcue, control patients will be gathered prospectively. The ED specialist will save the patient-number of eligible patients in the care pathway (before it is implemented). The specialist in charge of the patient is allowed to use patient data for research, without consent when data is anonymised. The specialist may grant this right to a third party, in this case the research team. This exchange of data has to be approved by the involved departments, which will be the department of Internal Medicine, Geriatrics and the Emergency Department.

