### **5.3 A SUMMARY OF THE NSC CARE PATHWAY**

1. Patients will be included in the care pathway by a general practitioner, elderly care physician or triagist at the ED. Their tasks include:
  - Check of inclusion and exclusion criteria
    - o guidelines of the study will be available on a card and in a digital format
  - Including patients via healthcare system or after contacting the specialist at the ED (internist, ED-doctor or elderly care physician)
  - Digital registration of a participant in the care pathway
2. The triagist or a trained nurse will perform the APOP, using the APOP-app on a tablet or in the electronic medical records. If possible, the ED-coordinator will assign an ED-coach to a participant of the study.
3. Every hospital will have their own system coupled to the Care Domain of the primary care provider and every participant will consent for sharing information on their frailty status. Patients will be seen by a doctor and a nurse. Three key players in this care pathway are:
  - I – Nurse
  - II – Specialist at the ED (specialist or resident in training):
    - a. in case of non-trauma patients: internist, emergency physician or elderly care physician
    - b. In case of trauma-patients: surgeon, orthopedist or emergency physician
    - c. preferably/ if possible no interns or untrained residents will see the patient with NSCIII
    - d. reviewing Frailty information from sources (primary care physician, informal caregiver, own findings, APOP; see also Appendix 1)

- ED-coach (if possible)
  - a. this can either be a secretary, nurse or a doctor
  - b. there is either no ED-coach, passive ED-coach or an active ED-coach
- 4. Tasks of the ED-coach (no ED coach, passive ED-coach or active ED-coach):
  - It is possible that no ED-coach can be appointed.

If an ED-coach can be appointed however, they can either be active or passive in patient care and perform the following tasks.

If a passive ED-coach is feasible:

- Checking progress at the ED for the participant every 30 minutes

If an active ED-coach is feasible:

- Coordinating care and communicating with the doctor and nurse taking care of the participant.
- Checking completeness of data for inclusion, reviewing medical history, calling the local responsible for medication verification <24 hours after admission, evaluating care at home, assess patient satisfaction for participant of the care pathway
  - o Checking progress at the ED for the participant every 30 minutes

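### Patient satisfaction is a main endpoint with a hypothesised improvement, but the protocol describes collecting it only from care-pathway participants, so the plan as written cannot test that hypothesis

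*Protocol*

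**What the plan says.** **Status of the endpoint.** Protocol section 1 (Summary): "Main endpoints are to evaluate the length of stay at the ED (ED-LOS) and exploring patient satisfaction on 4 established domains". Section 3 lists ED-LOS and satisfaction on four domains together under the primary objectives, which "of the care pathway are to evaluate" those two items. Section 5.4.1 includes satisfaction among the endpoints. Section 2 gives the direction expected: "We hypothesize that the care pathway will primarily improve patient satisfaction and reduce the ED-length of stay".

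**Collection.** Section 5.2, under the patient satisfaction heading: "Patient satisfaction will be evaluated for each participant of the care pathway, directly after the patient leaves the care pathway". Section 5.3 adds, among the tasks of an active ED-coach where one is feasible: "assess patient satisfaction for participant of the care pathway".

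**Controls.** Section 5.1.4 says of the retrospective CTcue controls: "These data will be retrieved anonymously according to our defined in- and exclusion criteria, study parameters and endpoints". For hospitals without CTcue it says: "The ED specialist will save the patient-number of eligible patients in the care pathway (before it is implemented"). It also states: "Controls will not be specifically asked for informed consent". Section 5.3.1 sets the intended comparison as each hospital's control group against its own intervention group.

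**The concern.** A prediction of improvement is a comparative claim, and the protocol's comparator is the pre-implementation control group in the same hospital. Yet both statements on how satisfaction is obtained refer to people in the pathway, and neither control route includes handing a patient a form. If the study runs as described, one of its two main endpoints will have scores from the intervention period and nothing to set against them. High scores in pathway participants could then be read as evidence that the pathway raised satisfaction, when they could equally be what usual care would have produced.

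This cannot be left to a statistical analysis plan. Who receives a questionnaire, and when, is a study procedure, and responses that were never collected cannot be recovered at analysis.

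A smaller concern is who takes the measurement. Where there is an active ED-coach, the person who coordinates the patient's care is also the one assigned to assess satisfaction.

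**Working it through.** **1. What the protocol's own size calculation covers.** The only planned sample size is in section 5.1.5 and concerns ED-LOS. Inputs: mean 3 h 20 min, reduction 10%, so the difference is 0.10 × 200 min = 20 min = 0.333 h; two-sided alpha 0.05; power 80%; equal groups. Formula: n per group = 2 × (1.960 + 0.842)² × SD² / difference².

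- SD printed as 1.17 and read as 1 h 17 min (1.283 h): n = 233 per group, 466 in total. This matches the protocol.
- SD read as decimal 1.17 h: n = 194 per group, 388 in total. This does not match.

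So the stated figure is reproduced from ED-LOS inputs alone. No effect size, standard deviation or sample size is given for satisfaction.

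**2. Where satisfaction responses can come from.**

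| Group | How patients enter | Contact described that could yield a form | Satisfaction responses as written |
|---|---|---|---|
| Pathway participants | Referral or ED triage, with consent (sections 1, 5.2) | Yes, on leaving the pathway (section 5.2) | Yes |
| Controls, CTcue hospitals | Retrospective, anonymous record retrieval (section 5.1.4) | None; the visit is over and the retrieved data are anonymous | None |
| Controls, other hospitals | Prospective; specialist saves the patient number (section 5.1.4) | None described; no individual consent sought | None described |

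**3. Could record retrieval supply it?** Section 5.1.4 says CTcue retrieval follows the defined endpoints, and section 5.4.1 lists satisfaction among them. But the visible items of the Appendix 2 form ask the patient to rate, for example, understanding of tests, reassurance, feeling safe and trust in staff during that ED visit. Nothing in the protocol says this form is used or filed in usual care. A record search cannot return answers that nobody was asked to give.

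**4. Consequence for the contrast.** The quantity implied by section 2 is the mean (or distribution) of scores in pathway participants minus that in controls. Its variance has one term for each group, of the form SD²/n. With no control responses, the control mean does not exist and the control term is undefined. More pathway participants do not help: reaching the target of 300 in that group leaves the difference as inestimable as 233 would.

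**5. Who assesses.** Section 5.3 allows no coach, a passive coach or an active coach, and assigns satisfaction only to the active one. Section 5.2 names no assessor. The mode of assessment may therefore differ between hospitals, and where the active coach does it, the assessor also delivers part of the intervention.

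**The case against.** **No sentence excludes controls.** True. That satisfaction is collected only in the pathway is inferred from the collection text. The protocol also uses the term care pathway loosely: its control-group section speaks of complications after a patient leaves the pathway and of eligible patients in a pathway not yet implemented. This weakens the argument from wording alone. It does not supply a procedure: no section gives controls the form, and the control follow-up assigned to the research nurse concerns complications.

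**Some controls are identified prospectively.** This stands, and it limits the point. A reader might infer that comparison with controls is impossible in principle. The documents do not support that: in hospitals without CTcue, the treating specialist identifies eligible patients as they present, and a form could be given to them. The step is absent, not impossible.

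**Satisfaction is exploratory.** The summary does speak of exploring it, and the sample size rests on ED-LOS alone. A reader might infer a confirmatory co-primary test with no power. The protocol never sets up such a test, so that reading goes too far. The predicted improvement in section 2 and the primary-objective label in section 3 still conflict with a purely exploratory aim.

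**An earlier study might be the comparator.** Section 5.2 cites one as the source of the four domains. It is not named as a comparison group, and section 5.3.1 makes the comparator each hospital's own controls.

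**The coach.** A reader might infer that pathway scores are inflated. The documents give no figure for this, the task applies only where an active coach is feasible, and the form has printed scales that a patient could complete alone. What stands is a possible upward bias at some sites.

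**Conclusion.** The point holds as a mismatch between aim and data collection. Satisfaction is a main endpoint and primary objective with a predicted improvement. Collection is described for pathway participants only. Anonymous retrospective controls cannot supply the answers, and no questionnaire step exists for prospective controls. Followed as written, the plan cannot estimate the between-group difference in satisfaction, so the predicted improvement can be neither confirmed nor contradicted. This affects one of the two main endpoints; ED-LOS and its sample size are untouched.

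The conclusion rests on two assumptions. The first is that the Appendix 2 form is not already part of usual ED care with answers filed in the record; nothing in the protocol says it is. The second is that the parts not visible in the text reviewed (the schematic in section 5.2, and items 1 to 4 and any instructions of Appendix 2) do not assign the form to controls. If they do, the operative sections need to say so, and the difficulty would remain for the CTcue hospitals.

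**What to change.** **Minimum change.** Keep ED-LOS as the only primary comparative endpoint. In sections 1, 2, 3 and 5.4, restate satisfaction as a descriptive outcome in pathway participants and remove the prediction that it will improve. In section 5.1.4, state that satisfaction is not among the endpoints retrieved for controls. This costs wording only.

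**If a comparison is wanted.** Give the same Appendix 2 form, at the same point on leaving the ED and with consent, to control-period patients in the hospitals that enrol controls prospectively, and compare within those hospitals only. This needs a consent procedure and some staff time there. The protocol does not say which hospitals have CTcue, so the number of controls this would reach is unknown: anywhere from none to the full target of 300. It also has to be decided promptly. Section 4 has control inclusion restarting in August 2020, dates its own text October 2020 and estimates implementation for January 2021. Responses given directly after the visit cannot be obtained once the control period has closed.

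**In either case.** Have the form self-completed in every hospital and take the assessment off the active ED-coach's task list in section 5.3, so that the method is the same whether or not a coach is present. The cost is small.

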### **5.3 A SUMMARY OF THE NSC CARE PATHWAY**

1. Patients will be included in the care pathway by a general practitioner, elderly care physician or triagist at the ED. Their tasks include:
  - Check of inclusion and exclusion criteria
    - o guidelines of the study will be available on a card and in a digital format
  - Including patients via healthcare system or after contacting the specialist at the ED (internist, ED-doctor or elderly care physician)
  - Digital registration of a participant in the care pathway
2. The triagist or a trained nurse will perform the APOP, using the APOP-app on a tablet or in the electronic medical records. If possible, the ED-coordinator will assign an ED-coach to a participant of the study.
3. Every hospital will have their own system coupled to the Care Domain of the primary care provider and every participant will consent for sharing information on their frailty status. Patients will be seen by a doctor and a nurse. Three key players in this care pathway are:
  - I – Nurse
  - II – Specialist at the ED (specialist or resident in training):
    - a. in case of non-trauma patients: internist, emergency physician or elderly care physician
    - b. In case of trauma-patients: surgeon, orthopedist or emergency physician
    - c. preferably/ if possible no interns or untrained residents will see the patient with NSCIII
    - d. reviewing Frailty information from sources (primary care physician, informal caregiver, own findings, APOP; see also Appendix 1)

- ED-coach (if possible)
  - a. this can either be a secretary, nurse or a doctor
  - b. there is either no ED-coach, passive ED-coach or an active ED-coach
- 4. Tasks of the ED-coach (no ED coach, passive ED-coach or active ED-coach):
  - It is possible that no ED-coach can be appointed.

If an ED-coach can be appointed however, they can either be active or passive in patient care and perform the following tasks.

If a passive ED-coach is feasible:

- Checking progress at the ED for the participant every 30 minutes

If an active ED-coach is feasible:

- Coordinating care and communicating with the doctor and nurse taking care of the participant.
- Checking completeness of data for inclusion, reviewing medical history, calling the local responsible for medication verification <24 hours after admission, evaluating care at home, assess patient satisfaction for participant of the care pathway
  - o Checking progress at the ED for the participant every 30 minutes
  - o Checking adherence to the recommended APOP-guidelines after completion

- 5. Tasks of the nurse:
  - Performing the APOP screening (potential)
  - Conventional care at the ED
  - Performing the ordered diagnostic tests
  - Performing actions following the APOP-risk score
- 6. Tasks of the doctor:
  - Conventional care at the ED
  - Ordering a standard set of diagnostics, at least: ECG, lab, urinalysis, X-thorax and bladder scan.
- 7. Actions following APOP-screening:
  - 1. Low risk, no supplementary actions recommended
  - 2. High risk of functional decline - the following actions are recommended among others; in case of suspected dehydration at presentation: starting early fluid administration, in case of admission: limiting the length of stay at the ED and organizing early transfer to the ward.
  - 3. High risk of cognitive decline - the following actions are recommended among others; Making sure the patient has a comfortable bed, has adequate lightning in the room and knows how to call for help.
  - 4. High risk of functional and cognitive decline - the following actions are recommended among others; consider the diagnosis delirium and an internist geriatric medicine or clinical geriatrician can be consulted for a comprehensive geriatric assessment after discharge from ED.
- 8. Discharge from the ED:
  - Possibilities include: admission to the ward, discharge to home, discharge to facility, discharge to short stay facility for primary care, discharge to geriatric rehabilitation.
  - Each study participant will be followed-up after leaving the care pathway.
  - A review of the medication list will be performed by the doctor at the ward, elderly care physician, the clinical pharmacologist or hospital pharmacist

- 9. Tasks of the research nurse / researcher:

- Collecting data for the database (see study parameters and endpoints)
- Collecting data for each participant 30 days after leaving the care pathway

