| 8. Denkt u dat u en/of uw klachten uitgebreider onderzocht hadden moeten worden?                                                      | 1                    | 2                   | 3            | 4                 | 5           | 6                |
| 9. Bent u tevreden over de totale duur van uw verblijf op de Spoedeisende Hulp?                                                       | 1                    | 2                   | 3            | 4                 | 5           | 6                |
| 10. Voelde u zich veilig tijdens uw verblijf op de Spoedeisende Hulp?                                                                 | 1                    | 2                   | 3            | 4                 | 5           | 6                |
| 11. Werd er door de zorgverleners naar u geluisterd tijdens uw verblijf op de Spoedeisende Hulp?                                      | 1                    | 2                   | 3            | 4                 | 5           | 6                |
| 12. Had u vertrouwen in de deskundigheid van de zorgverleners op de Spoedeisende Hulp?                                                | 1                    | 2                   | 3            | 4                 | 5           | 6                |
|                                                                                                                                       | Zeer slecht   |                     |              |                   |             | Zeer goed |

13. Welk cijfer zou u de Spoedeisende

Hulp geven op een schaal van 0-  
10?

0      1      2      3      4      5      6      7      8      9      10

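### The active ED-coach, who coordinates the patient's care under the pathway, is also assigned to assess that patient's satisfaction, a main endpoint, and no specific assessor is named for the other participants

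*Protocol*

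**What the plan says.** The Summary makes satisfaction a main endpoint: "Main endpoints are to evaluate the length of stay at the ED (ED-LOS) and exploring patient satisfaction on 4 established domains". Section 3 lists it as a primary objective, and section 2 hypothesises that the pathway will improve it.

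The coach belongs to the intervention. The Summary says under Intervention: "If feasible, an ED-coach (passive or active form) will be appointed to each participant of the care pathway". Section 5.3, item 4, describes three situations:

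- **Active coach.** The tasks include "Coordinating care and communicating with the doctor and nurse taking care of the participant" and, further down the same list, "evaluating care at home, assess patient satisfaction for participant of the care pathway".
- **Passive coach.** One task is listed: "Checking progress at the ED for the participant every 30 minutes".
- **No coach.** The item allows for this: "It is possible that no ED-coach can be appointed".

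Section 5.2, under the heading on patient satisfaction, sets the coverage without reference to a coach: "Patient satisfaction will be evaluated for each participant of the care pathway, directly after the patient leaves the care pathway". Section 5.3, item 9, asks the research nurse or researcher to collect the data on study parameters and endpoints. Both lists in section 5.4.1 include patient satisfaction.

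The questionnaire at the end of the protocol has patient-rated items on a 1 to 6 scale. One asks whether the caregivers listened: "Werd er door de zorgverleners naar u geluisterd tijdens uw verblijf op de Spoedeisende Hulp". Others cover reassurance, feeling safe, confidence in the caregivers' expertise and satisfaction with the length of the ED stay. The last is a mark from 0 to 10 for the ED.

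**The concern.** A satisfaction score is open to influence from whoever asks for it. A patient aged 70 or over who has just been looked after by a coach, and is then asked by that coach how the ED stay went, may give a kinder answer than on a form filled in alone. Satisfaction is a main endpoint with a hypothesised improvement, so the likely error runs in the hoped-for direction.

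A second issue is uniformity. If one person collects the form for actively coached patients and someone unspecified collects it for the rest, scores and completeness may vary with coach status for reasons unrelated to how satisfied patients are. Coach status depends on local feasibility, so it may also be tied to hospital and workload.

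**Working it through.** The protocol gives no figure for satisfaction: no expected score, standard deviation, detectable difference or power. The sample size in section 5.1.5 concerns ED length of stay only. The point therefore rests on setting the sections side by side.

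**1. Does the assessor also deliver the intervention?** Yes, for the active coach. Section 5.3, item 4, puts coordination of care and assessment of satisfaction in the same task list. Section 6.2 adds that a coach, where feasible, introduces the patient to the pathway and sees that the special care is given.

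**2. Does the form ask about things the coach can influence?** Yes. Being listened to, feeling safe, reassurance and the duration of the stay are all close to what a coordinating coach is there to improve.

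**3. Is independent or unaided completion required?** No section in the text at hand says so. The questionnaire as available starts at item 5, so instructions above it cannot be judged and are not counted as missing.

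**4. Who is named to assess satisfaction?**

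| Patient's situation | Named assessor | General provision |
|---|---|---|
| Active coach | The coach (5.3, item 4) | 5.2 coverage; research nurse (5.3, item 9) |
| Passive coach | None | Same |
| No coach | None | Same |

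The task lists of the ED nurse and the doctor (5.3, items 5 and 6) do not mention satisfaction. Item 9 covers endpoint data in general but does not say that the research nurse administers the form; its only timed duty is at 30 days. Section 5.2 requires the form directly after the patient leaves the pathway.

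**5. Could the effect of the assessor be examined later?** Not assuredly. The parameter list in section 5.4.1 includes neither coach level nor who helped with the form.

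**6. How large could the bias be?** Let *p* be the share of pathway participants with an active coach, *b* the mean shift in score when that coach asks the questions, and *c1* and *c0* the proportions of forms completed with and without an active coach. The shift in the pathway mean is

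*b* × *p c1* / (*p c1* + (1 − *p*) *c0*).

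With equal completion (*c1* = *c0*) this reduces to *p* × *b*. The protocol gives none of these quantities, and *p* may lie anywhere from 0% to 100%. The shift therefore lies between zero and *b*, and *b* is unknown. No numerical size can be derived.

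**The case against.** Several arguments weaken stronger versions of this point, and most of them stand.

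- **Coverage.** A reader might infer that satisfaction is collected only where staffing permits an active coach. The documents do not support this. Section 5.2 requires it for each pathway participant, and item 9 gives endpoint data to the research nurse or researcher. What remains is that the specific task is named for one role only.
- **Meaning of the task.** The ratings are the patient's own. The protocol does not say whether the coach interviews the patient, hands over the form or merely checks that it comes back. The coach may be a secretary, who is not clearly one of the caregivers being rated. This lowers the likely bias but does not remove it: an active coach of any profession still coordinates the patient's care.
- **Size.** A reader might infer that the shift could by itself look like a treatment effect. That needs assumptions about the score's spread, the shift and the share of actively coached patients, none of which the protocol supplies. The shift is also diluted by every participant without an active coach.
- **Between-group bias.** A reader might infer a difference in mode between pathway and control patients. No section describes surveying controls for satisfaction, and part of the control data is retrieved retrospectively from records. That inference would rest on a comparison the protocol does not set out.
- **Permanence.** A reader might conclude that the bias is beyond later repair. That is too strong: if coach level and help with the form were recorded, it could at least be explored. As written, that record is not assured.
- **Staffing.** No section places the research nurse in the ED when the patient leaves, so making that nurse the required administrator might need extra staff. This argues for self-completion.

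**Conclusion.** The point holds in limited form. For patients with an active ED-coach, the protocol assigns a person who delivers part of the intervention to assess a main endpoint, on a form about the caregivers and the ED stay, with no stated safeguard. This is a real risk of courtesy bias towards the pathway. For other participants the protocol promises the same data but names no specific assessor, so the mode of collection may differ by coach status.

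The size cannot be given. The direction rests on the ordinary expectation that patients answer more kindly to someone who has cared for them; the protocol has no data on this. ED length of stay is untouched. The change is worth making because it is cheap and concerns study conduct, which section 5.3 itself fixes.

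**What to change.** Reconcile the satisfaction paragraph in section 5.2 with items 4 and 9 of section 5.3:

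1. Delete the satisfaction task from the active coach's list in item 4.
2. State that the Appendix 2 form is self-completed, with help where needed from a relative or a person not involved in the patient's care.
3. Apply the same mode and timing to every surveyed patient, whatever the coach level.
4. Add two fields to the data collected under section 5.4.1: coach level (none, passive, active) and who, if anyone, helped to complete the form.

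The cost is a wording change and two data fields; the form already exists. Self-completion with help from a relative needs no extra staff, and administration by the research nurse should not be made the required route. The downside is that somewhat more forms will probably be missing when nobody at the bedside is charged with obtaining them. The option of help limits this loss, and completion should be reported by coach level.
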